### *Mental wellbeing*

Patients will complete the 14-item hospital anxiety-depression score (HADS) (46) at baseline and 12-week follow-up. The 14-item instrument is comprised of a depression subscale and anxiety subscale which are each assessed through 7-items. Respondents are asked to rate their mental and emotional state over the past week. The HADS has good validity in community and clinical populations (47).

### *Patient activation*

The Patient Activation Measure (PAM®) (48) measures patients' knowledge, skills and confidence in managing their condition. PAM licences are available from NHS England and Improvement as part of the Supported Self-management component of the Personalised Care

Programme. At baseline and 12-week follow-up patients will respond (strongly disagree/disagree/agree/strongly agree/N/A) to 13 statements related to their confidence in managing their health. Patients' PAM score (0 - 100) will place them within one of four activation categories, providing insight into a range of health-related characteristics and behaviours. The PAM has been validated for use in adults with long term conditions (49-51).

### *Resource utilisation*

The case report forms (CRF) will measure the resource utilisations by each patient. The CRF will be administered to each patient at baseline and 12-week follow-up in both arms of the trial asking them to report any health care resources they have utilised in the preceding 12 weeks. Unit costs from secondary sources will be applied to the resources utilised to generate costs incurred by each patient.

## **10. STUDY POWER**

As per good practice recommendations for pilot studies (52), we will aim to recruit 30 patients to each arm and obtain a total sample of 60 participants. Findings of the current study will be used to inform the power calculations of future definitive RCTs.

## **11. DATA ANALYSIS**

Primary outcome data will be reported as descriptive statistics, including rates of: patient screening, eligibility, recruitment and retention to 12-week follow-up and survey completion. Qualitative interview data will be analysed thematically to generate themes. Exploratory between-group analyses will be conducted to determine preliminary intervention effectiveness. Normality and homogeneity of variance will be performed using the Shapiro-Wilks and Levene tests, respectively. For comparison of the variables at the pre-intervention, we will perform a one-way ANOVA. To analyze the responses before and after the intervention period, two-way analysis of variance for repeated measures will be used, with the main factors being the group (and the time (pre and post intervention) with Newman-Keuls post-hoc test. The level of significance will be set at  $P < 0.05$ .

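### Section 11 fixes a two-way repeated-measures ANOVA without naming the treatment contrast; ANCOVA on baselines already collected is clearer and more precise

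*Protocol*

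**What the plan says.** Section 11 of the protocol describes the comparison of arms in general terms: "Exploratory between-group analyses will be conducted to determine preliminary intervention effectiveness". It then fixes the method.

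- Baseline: "For comparison of the variables at the pre-intervention, we will perform a one-way ANOVA".
- Before and after: "two-way analysis of variance for repeated measures will be used, with the main factors being the group" and time, where time has two levels, "pre and post intervention) with Newman-Keuls post-hoc test".
- Threshold: "The level of significance will be set at" P < 0.05.

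The section names no group-by-time interaction and no adjustment for baseline.

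Section 10 sets the size, "we will aim to recruit 30 patients to each arm and obtain a total sample of 60 participants", on good-practice guidance for pilots rather than on a power calculation. It gives the later use of the data: "Findings of the current study will be used to inform the power calculations of future definitive RCTs".

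Section 9.2 measures the 6-minute walk, WIQ, WELCH, VascuQoL-6, EQ-5D-5L, AUDIT-C, smoking status, HADS and PAM once at baseline and once at 12 weeks. It states no pre-randomisation measurement for Fitbit activity or sleep, and no time points for the dietary questionnaire.

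**The concern.** The protocol goes as far as naming the model, the post-hoc procedure and the significance level, but it does not identify the quantity that answers the trial's between-arm question. A two-way repeated-measures ANOVA yields a group effect, a time effect and an interaction, and these mean different things in a randomised pre/post design. Two analysts could follow section 11 faithfully and report different treatment effects.

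Even on the most favourable reading, where the interaction is the test, the plan uses the baseline value less efficiently than it could. In a pilot of 60 whose findings are to inform a definitive trial, a clearly defined estimate with a narrower interval is worth having when it needs no new data.

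The two accompanying steps add little. Newman-Keuls on the group-by-time means includes comparisons that are not between arms. The baseline ANOVA tests whether randomised arms differ in expectation, which is already known to be false if randomisation was done properly.

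**Working it through.** **Inputs from the protocol.** Two arms, 1:1 (section 7.5); 30 per arm, 60 in total, and 2 × 30 = 60 agrees (section 10); one baseline and one 12-week value (section 9.2); significance level 0.05 (section 11), taken as two-sided. The protocol gives no power, effect size, SD or dropout figure, so there is no stated power to reproduce.

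**Assumptions.** A 12-week effect of 0.5 SD, the same SD (set to 1) at both visits, pre/post correlation rho from 0.3 to 0.9, all 30 per arm analysed, and baseline taken before allocation (section 7.3 places baseline at the consent visit).

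**1. Interaction against ANCOVA.** With two visits the interaction is the between-arm difference in mean change. Per-patient variances are:

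- interaction: 2(1 − rho)
- ANCOVA: 1 − rho² = (1 − rho)(1 + rho)
- ratio ANCOVA/interaction: (1 + rho)/2

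Power is approximately Φ(0.5/√(2V/30) − 1.96), where V is the variance above.

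| rho | V, ANCOVA | V, interaction | Ratio | Power, ANCOVA | Power, interaction |
|---|---|---|---|---|---|
| 0.3 | 0.91 | 1.40 | 0.65 | 52.8% | 37.3% |
| 0.5 | 0.75 | 1.00 | 0.75 | 60.9% | 49.1% |
| 0.7 | 0.51 | 0.60 | 0.85 | 77.4% | 70.5% |
| 0.8 | 0.36 | 0.40 | 0.90 | 89.8% | 86.5% |
| 0.9 | 0.19 | 0.20 | 0.95 | 99.3% | 99.1% |

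Worked line for rho 0.5: ANCOVA 0.5/√(1.5/30) = 2.236, less 1.96 = 0.276, Φ = 0.609. Interaction 0.5/√(2/30) = 1.936, less 1.96 = −0.024, Φ = 0.491.

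A simulation of 20,000 trials per setting, using t critical values, gave slightly lower power and the same ordering: 59.2% v 47.9% at rho 0.5, 75.1% v 69.0% at 0.7, 88.5% v 85.7% at 0.8. With no true effect the interaction rejected 4.9% to 5.1% of the time, so it is valid.

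For 80% power at rho 0.5, ANCOVA needs 48 per arm and the interaction 63. The 95% CI half-widths at 30 per arm are 0.438 v 0.506 SD at rho 0.5, and 0.361 v 0.392 SD at rho 0.7.

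**2. The group main effect, if it were read as the treatment test.** It averages the two visits. Randomisation makes the expected baseline difference zero, so the expected value is (0 + 0.5)/2 = 0.25 SD, half the 12-week effect (simulated 0.249 to 0.251).

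**3. The time main effect.** It pools the arms and compares before with after, so it is not a treatment comparison.

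**4. Newman-Keuls on the cell means.** Two groups by two times give four means and 4 × 3/2 = 6 pairs. Two are within-arm before/after comparisons, two cross both arm and time, one compares arms at baseline, and one compares arms at 12 weeks. Only the last is a between-arm comparison after treatment, and it makes no use of baseline.

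**5. Baseline tests.** Under proper randomisation each is significant 5% of the time whatever the trial does. With 10, 15 or 20 independent variables (assumed counts), the chance of at least one is 1 − 0.95^k = 40%, 54% or 64%.

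**The case against.** The best defence is that group and time are listed as the factors of the model, not as the tests of interest. A two-way repeated-measures ANOVA ordinarily includes the interaction, and the stated purpose of analysing responses before and after fits it. The sentence also has an unclosed bracket, so some wording may be lost. This defence largely stands: if the interaction is meant, the target is right, the test is unbiased, and only efficiency is lost, little of it when rho is high.

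A reader might therefore go too far in several directions:

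- **That the plan will halve the treatment effect.** This holds only if the group main effect is taken as the treatment test, and section 11 never designates it as such. The fault is that the contrast is unnamed.
- **That an effect will be claimed because one arm improves significantly and the other does not.** Section 11 plans no separate paired tests and states no such rule. Newman-Keuls makes the comparison available, no more.
- **That baseline tests will steer the analysis.** No decision is attached to them.
- **That the definitive trial will be wrongly sized.** Section 10 says that findings will inform its power calculation, not that the ANOVA estimate will be used. Outcome SDs and correlations can be taken from the same data under either analysis.
- **That every outcome has a baseline for ANCOVA.** Fitbit activity and sleep have none stated: the devices are issued as part of each arm's care (sections 8 and 8.1). Diet has no stated timing.

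It is also fair to say that nothing primary depends on this: the primary outcomes are feasibility and acceptability, and the sample of 60 does not rest on this test.

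**Conclusion.** The point holds as a low-to-moderate improvement, not as an error that undermines the pilot. Section 11 fixes a model without naming the contrast that estimates the treatment effect, and adds two steps that do not help to estimate it. On the favourable reading, ANCOVA gains about 12 percentage points of power at rho 0.5, 7 at 0.7 and 3 at 0.8, for an assumed 0.5 SD effect with 30 per arm. The variance ratio (1 + rho)/2 does not depend on the effect size or on n, but it does assume equal SDs at the two visits. Dropout would lower both power figures. An unseen statistical analysis plan might name the contrast, but the method is written into the protocol, so the protocol text should be corrected too.

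**What to change.** Reword section 11 as follows.

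- For each continuous outcome with a pre-randomisation baseline (6-minute walk outcomes, WIQ, WELCH, VascuQoL-6, EQ-5D, HADS, AUDIT-C, PAM), compare the 12-week value between arms as randomised by ANCOVA with the baseline value as covariate. Report the adjusted mean difference with its 95% CI.
- Report smoking status as a risk difference with 95% CI.
- For Fitbit activity and sleep, and for diet if no baseline is taken, report the between-arm difference with 95% CI without a baseline covariate.
- Delete the Newman-Keuls step and the baseline one-way ANOVA, and tabulate baseline characteristics by arm descriptively.

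The cost is a change of wording and one residual degree of freedom per ANCOVA model. No extra data, visits or patients are needed.

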## **12. HEALTH ECONOMICS**

The trial will not be adequately powered to conduct a formal health economic evaluation, therefore the data accrued from the pilot trial will be reported using descriptive statistics to explore the differences in resource utilisations, costs and effects between the trial arms. We will also assess the completion rates for the health economics data collection tools, responses for each question and health state utility values. At baseline and 12-week follow-up, all patients will complete the following:

- EuroQol's EQ-5D-5L and EQ-5D VAS questionnaire
- Case report forms measuring health resource utilisation

## **13. STUDY MONITORING**

- This is a low risk study and major safety issues are not anticipated.
- The study may be subject to inspection and audit by the study sponsor (NUTH).
- This is to ensure that the study is conducted to a high standard in accordance to the protocol, the principles of GCP, relevant regulations, guidelines and with regard to patient safety.

## **14. SERIOUS ADVERSE EVENT MONITORING AND REPORTING**

- RECs require all serious adverse events to be reported. We do not anticipate any major risks or adverse events from this study.
- Should they occur they will be recorded during visits and categorised as to relatedness and severity
- The NUTH NHS Trust will be informed according to trust policy

## **15. ETHICS AND REGULATORY ISSUES**

- Ethical approval from a local REC and R&D bodies will be obtained prior to the commencement of the study.
- Written confirmation of approval will be received before the study commences
- Participant Information Sheets (PIS) will be provided to eligible participants (clinicians and patients) and written informed consent will be obtained prior to any study procedures being undertaken.

## **16. PATIENT AND PUBLIC INVOLVEMENT**

With the time constraints around COVID19 and the issues concerning group-based discussions, PPI groups have been difficult to undertake. However, we have performed a small PPI group among patients with PAD to determine the face-acceptability and value of the intervention.

## **17. CONFIDENTIALITY & DATA HANDLING**

- Personal data will be regarded as strictly confidential
- Identifiable data e.g. name, date of birth and consent form, will be stored separately to study data
- An NHS computer will be used for all inputting of data onto a database. This will be password protected and have IT security measures offered by the Freeman Hospital IT department.
- To preserve anonymity, any data leaving the study site will identify participants by a unique study identification code
- The study will comply with the Data Protection Act 1998 and Caldicott Principles
- All study records and investigator Site Files will be kept at site in a locked filing cabinet with restricted access

## **18. INFORMATION GOVERNANCE/DIGITAL PLATFORM**

- All patients will be consented to transfer data via nhs.net email between NUTH and Healthworks as this is necessary for the running of the study.
- Data will be stored on the REDCAP system
- The data transferred via the fitbits will only contain the patients' unique study identification code and no other patient identifiable data.
- Fitabase resides on Microsoft Azure platform. It relies on robust security, both physical on-premise guarding and over network provided as part of the platform. Windows Azure runs in data centres managed and operated by Microsoft Global Foundation Services (GFS). These geographically dispersed data centres comply with key industry standards such as ISO/IEC 27001:2005 for security and reliability. They are managed, monitored and administered by Microsoft operations staff that have years of experience in delivering the world's largest online services with 24:7 continuity. In addition to data centre, network and personnel security practices, Windows Azure incorporates security practices at the

application and platform layers to enhance security for service administrators. In addition to primary copies of the databases, Small Steps Labs LLC maintains snapshot archives of database for disaster recovery purposes. Backup copies reside only on hardware and are encrypted and password protected.

## **19. INSURANCE AND FINANCE**

- The Newcastle upon Tyne Hospitals NHS Trust has liability for clinical negligence that harms individuals toward whom they have a duty of care
- NHS Indemnity covers NHS staff conducting the trial for potential liability in respect of harm arising from the conduct of the study.
- Grant from League of Friends of Freeman Hospital and departmental resources are funding the project

## **20. STUDY REPORT/PUBLICATIONS**

- Publication will be the responsibility of the PI and co-applicants
- Authorship principles will follow the International Medical Editors conventions as follows: Each author should have participated significantly in the work to take responsibility for the content. This participation should include (a) conception or design, or analysis and interpretation of data, or both; (b) drafting the article or revising it for critically important content; and (c) final approval of the version to be published.
- The outcomes of this study will be published in peer review journals and presented at local, national and international meetings and conferences
- Individuals will not be identified from any study report
- A lay summary of the results will be available for all study participants

## **21. INTELLECTUAL PROPERTY**

This study will generate work that will have intellectual property. Any materials developed will be copyrighted as per Trust property. We will not sell any materials for profit however we will require any user to acknowledge the source of materials.

## 22. STUDY MILESTONES

[figure not shown]

**23. GANTT CHART**

|                                       | 2020 |     |     |     |     |     |     | 2021 |     |     |     |     |     |     |     |     |     |     |     |
|---------------------------------------|------|-----|-----|-----|-----|-----|-----|------|-----|-----|-----|-----|-----|-----|-----|-----|-----|-----|-----|
|                                       | Jun  | Jul | Aug | Sep | Oct | Nov | Dec | Jan  | Feb | Mar | Apr | May | Jun | Jul | Aug | Sep | Oct | Nov | Dec |
| Protocol development                  |      |     |     |     |     |     |     |      |     |     |     |     |     |     |     |     |     |     |     |
| Sponsorship application               |      |     |     |     |     |     |     |      |     |     |     |     |     |     |     |     |     |     |     |
| Ethics application                    |      |     |     |     |     |     |     |      |     |     |     |     |     |     |     |     |     |     |     |
| PIS and consent form development      |      |     |     |     |     |     |     |      |     |     |     |     |     |     |     |     |     |     |     |
| Sponsorship confirmation              |      |     |     |     |     |     |     |      |     |     |     |     |     |     |     |     |     |     |     |
| Ethics approval                       |      |     |     |     |     |     |     |      |     |     |     |     |     |     |     |     |     |     |     |
| ARC funding application               |      |     |     |     |     |     |     |      |     |     |     |     |     |     |     |     |     |     |     |
| Intervention materials development    |      |     |     |     |     |     |     |      |     |     |     |     |     |     |     |     |     |     |     |
| Research nurse hired                  |      |     |     |     |     |     |     |      |     |     |     |     |     |     |     |     |     |     |     |
| Purchasing of Fitbits and tablets     |      |     |     |     |     |     |     |      |     |     |     |     |     |     |     |     |     |     |     |
| Health Trainers assigned to study     |      |     |     |     |     |     |     |      |     |     |     |     |     |     |     |     |     |     |     |
| Patient screening                     |      |     |     |     |     |     |     |      |     |     |     |     |     |     |     |     |     |     |     |
| Patient recruitment                   |      |     |     |     |     |     |     |      |     |     |     |     |     |     |     |     |     |     |     |
| Baseline assessments                  |      |     |     |     |     |     |     |      |     |     |     |     |     |     |     |     |     |     |     |
| Intervention/usual care               |      |     |     |     |     |     |     |      |     |     |     |     |     |     |     |     |     |     |     |
| Follow-up assessments                 |      |     |     |     |     |     |     |      |     |     |     |     |     |     |     |     |     |     |     |
| Quantitative data cleaning            |      |     |     |     |     |     |     |      |     |     |     |     |     |     |     |     |     |     |     |
| Quantitative data analysis            |      |     |     |     |     |     |     |      |     |     |     |     |     |     |     |     |     |     |     |
| Interviews                            |      |     |     |     |     |     |     |      |     |     |     |     |     |     |     |     |     |     |     |
| Interview data transcription          |      |     |     |     |     |     |     |      |     |     |     |     |     |     |     |     |     |     |     |
| Thematic analysis of qualitative data |      |     |     |     |     |     |     |      |     |     |     |     |     |     |     |     |     |     |     |
| Dissemination events                  |      |     |     |     |     |     |     |      |     |     |     |     |     |     |     |     |     |     |     |
| Report writing                        |      |     |     |     |     |     |     |      |     |     |     |     |     |     |     |     |     |     |     |

